### Recruitment

Patients will be recruited by the representatives of the ulcer commission of the health region or, in the absence of such a figure, the person appointed for this in each of the participating centres. Before starting the study, all those involved will be contacted to explain the study methodology.

The recruitment process is to start in the treatment rooms of the health centres (Figure 1). Each of aforementioned individuals responsible for this process will have access to the necessary information for consecutively recruiting patients in line with the inclusion and exclusion criteria. When eligible patients are identified, the nurses will explain the possibility of their inclusion in the study and if they agree to participate, they will be referred to the assigned outpatient clinic, a corresponding appointment being arranged for them.

**Figure 1 Fig1:**
[figure not shown]
**Study algorithm.**

Patients will have an appointment in the health center; they will be seen by a doctor of the centre, who will carry out an interview to collect data related to the selection check list, and they will be weighed, their height measured, and a ABI test will be performed. If the patient meets the inclusion criteria, they or their legal guardian will be asked to give verbal and written informed consent before inclusion in the clinical trial, and after a “Patient Information Sheet for research projects involving the use of biological samples” has been provided and explained to them, by the principal investigator.

Once patients give informed consent, the doctor will contact the Primary Care Research Unit of Bizkaia to request that the patient be randomly allocated to the control or intervention group, and their inclusion in the study will be reported to their general practitioner. The patient’s wound will be cared for as usual, and they will be given a patient handbook including a diary to keep a daily record of their experiences and any adverse effects, and an appointment will be made for their first treatment as part of the study, either using autologous PRP or under the MWC protocol, depending on their group allocation. The patient handbook also includes a telephone number they should call in the event of any unforeseen problems between treatments.

In the event that there is no record in a patient’s medical record of a blood test having been performed in the 6-months prior to inclusion in the study, the general practitioner will request a blood test, the results of will be taken as the baseline measurement.

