**Table 2 Tab2:** **Timetable for the intervention group**

**Activities**	**Recruitment Day 0**	**Selection Day 1**	**Day 3**	**Day 5**	**Day 8**	**Day 15**	**Day 22**	**Day 29**	**Day 36**	**Day 43**	**Day 50**	**Day 57**	**Day 64**
Patient recruitment	X												
1^st^ visit		X											
Leg Doppler ultrasound		X											
Informed consent		X											
Randomisation		X											
Inform GP in writing		X											
Conventional treatment		X	X	X									
Autologous PRP treatment					X	X	X	X	X	X	X	X	
Ulcer Assessment					X				X				X
Final Assessment													X

Week^(1)^: the wound will be treated every 48 to 72 hours during these weeks, as required in each case (depending on the condition of the ulcer).

Week^(1)^: the wound will be treated every 48 to 72 hours during these weeks, as required in each case (depending on the condition of the ulcer).

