### Intervention group

Patients in the intervention group will receive wound care once a week with autologous PRP, based on the estimated mean lifespan of platelets (7–10 days). The treatment with autologous PRP will be performed in the assigned outpatient clinic, in the phlebotomy room, by qualified nurses ([name]).

As in the control group, the nurse will be responsible for making appointments for the next treatment and will collect data to be entered in an Access database by the administrator. The first treatment session of the study will be performed on day 8, and the data will be recorded in the patient medical record. From this point onwards, data will be collected every 7 days for 9 weeks. Treatment schedule for the PRP group is shown in Table 2.

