### Outcome measures

#### Reduction in ulcer size

A main variable, in terms of the difference in the surface area of the ulcer at weeks 5 and 9 of treatment compared to baseline, expressed as the percent reduction in area for each of the patients in the intervention and control groups.

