#### Ulcer area

Surface area of the ulcer, expressed in square centimetres and measured at baseline and at weeks 5 and 9, using the ImageJ software to analyse photographs taken at these time points.

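### The baseline ulcer area, which is the denominator of the primary outcome, is measured on Day 8, a week after open randomisation on Day 1, and the timing of the eligibility blood test relative to randomisation is unclear

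*Protocol article*

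**What the plan says.** **Allocation.** Under Recruitment, Study algorithm, "Once patients give informed consent, the doctor will contact the Primary Care Research Unit of Bizkaia to request that the patient be randomly allocated". In Tables 1 and 2 the row "Randomisation" is marked on Day 1, together with the first visit and consent.

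**The week that follows.** "The patient’s wound will be cared for as usual, and they will be given a patient handbook". Both tables show conventional treatment on Days 1, 3 and 5. The Intervention group section then says "The first treatment session of the study will be performed on day 8".

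**Baseline area.** The row "Ulcer Assessment" is marked on Days 8, 36 and 64 only. The main variable is the change in area at weeks 5 and 9 "compared to baseline, expressed as the percent reduction in area for each of the patients in the intervention and control groups". Area is "measured at baseline and at weeks 5 and 9, using the ImageJ software to analyse photographs taken at these time points". The Statistical analysis section compares the percent reductions by intention to treat and then fits covariance models adjusted for baseline.

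**Blinding.** The Limitations section states that patients and researchers will know the group. An independent person reads the photographs without patient or group data.

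**Blood results.** The Inclusion criteria require normal counts and negative serology, and the Study algorithm makes consent conditional on the inclusion criteria being met. For a patient with no test on record in the 6 months before inclusion, "the general practitioner will request a blood test, the results of will be taken as the baseline measurement". Neither table has a row for a blood test.

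**The concern.** Anything used as a baseline should be fixed before the arm is known, so that allocation cannot influence it. Here the order is reversed for the quantity that divides the primary outcome. Three things are at stake.

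- **Care.** In an open-label trial, wound care and patient behaviour during the week after allocation can differ by arm even where the schedule is the same. A change in area before Day 8 alters the denominator, and the same value is then used as the adjustment covariate.
- **Loss.** A patient who leaves between Day 1 and Day 8 belongs to the randomised population but has no scheduled baseline photograph. Such losses could differ by arm, since one arm is waiting for repeated blood draws.
- **Patient-reported baseline.** The CIVIQ section puts the baseline questionnaire in the baseline treatment session, so it too is answered by patients who know their arm.

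Separately, if a requested blood result can come back after the call, an eligibility decision could follow allocation. The withdrawal section takes out patients who meet an exclusion criterion during the study.

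**Working it through.** **1. Which day is baseline?** Day 8 is the only ulcer assessment before Day 36 in either table, and it is the day of the first study treatment. Days 36 and 64 fall 36 - 8 = 28 and 64 - 8 = 56 days later, which is weeks 5 and 9 if Day 8 opens week 1. They are also 36 - 1 = 35 and 64 - 1 = 63 days after Day 1, that is, five and nine elapsed weeks from randomisation. The week labels alone therefore do not settle the matter, but the assessment marks do: no area measurement is scheduled on Day 0 or Day 1. Table 1 carries the same day marks as Table 2, so this applies to both arms.

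**2. Gap.** Randomisation to baseline area: 8 - 1 = 7 days, with allocation known throughout.

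**3. Effect on the percent reduction (illustration).** Let r be the reduction at the final assessment relative to the Day 1 area, and c the proportional change in area from Day 1 to Day 8. With the final area held fixed,

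reported reduction = 1 - (1 - r)/(1 + c).

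For r = 0.50 and c = -0.10: 1 - 0.50/0.90 = 44.4%, a shift of -5.6 points. For c = +0.10: 1 - 0.50/1.10 = 54.5%, a shift of +4.5 points. The protocol gives no value for c, so the table shows an assumed range, as reported percent with the shift in points.

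| Reduction from Day 1 | c = -10% | c = -5% | c = +5% | c = +10% |
|---|---|---|---|---|
| 30% | 22.2 (-7.8) | 26.3 (-3.7) | 33.3 (+3.3) | 36.4 (+6.4) |
| 50% | 44.4 (-5.6) | 47.4 (-2.6) | 52.4 (+2.4) | 54.5 (+4.5) |
| 70% | 66.7 (-3.3) | 68.4 (-1.6) | 71.4 (+1.4) | 72.7 (+2.7) |

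These become shifts in the comparison only if the change occurs in one arm and not the other. A change common to both arms scales the remaining-area ratio by the same factor and cannot create a difference where there is none. If the early change carried through proportionally to the final area, the reduction from Day 8 would be unaffected.

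The Sample size section plans for a difference of 15 points, read here as percentage points of area reduction, which is an assumption. On that reading, 5.6/15 = 37% and 4.5/15 = 30% of the design difference.

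**4. Loss before Day 8.** With 75 per arm, each 5% lost is 0.05 × 75 = 3.75, about 4 patients per arm. The 5% is an assumption, as the protocol gives no rate for this week. The sample size allows for 30% withdrawal overall, so power suffers only if total loss exceeds that. A difference in loss between arms matters whatever the total.

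**5. Blood test, statements side by side.** (a) Inclusion requires blood results. (b) Consent follows if inclusion is met. (c) Randomisation follows consent, on the same day. (d) If no recent test exists, one is requested, with no timing given. Statements (a) to (c) imply results before allocation. Statement (d), with no blood test in the timetable, leaves open that the result comes later.

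**The case against.** The case on the other side has real force on several points.

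- **Day 8 is a natural start-of-treatment baseline.** The outcome is defined by weeks of treatment, treatment starts on Day 8, and a Day 1 baseline would add a week of non-study care to both arms. This stands as a reason to want a measurement on Day 8. It does not explain why allocation must come before it.
- **Early allocation serves a purpose.** A reader might infer that randomising on Day 1 gains nothing, since scheduled care is the same until Day 8. The documents do not support that: the first appointment is made according to allocation, and the two treatments are given in different rooms by different staff.
- **Masked reading and equal scheduled care limit bias.** Both lower the risk. Neither controls how care is actually delivered in that week, nor who is still present for the Day 8 photograph.
- **The blood-test sentence.** A reader might infer that ineligible patients are randomised and then removed. The text does not state that sequence. Consent is conditional on the inclusion criteria, the test is tied to the period before inclusion, the tables also omit other procedures such as CIVIQ, and the algorithm figure is not shown. What remains is an ambiguity.
- **Intention to treat.** It would go too far to say that patients lost before Day 8 cannot be analysed. The 20 cm² limit implies some area estimate at selection, and handling of missing baselines may be set out in an analysis plan that is not shown.

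**Conclusion.** The point holds for the order of events: both tables place the baseline area, and so the primary denominator and the covariate, 7 days after open allocation. This is avoidable in an open-label trial and worth correcting.

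No bias has been demonstrated and its size is unknown. The figure of 5.6 points should not be read as an expected error. It assumes a 10% shrinkage in one arm only, before any platelet-rich plasma is given, in ulcers that have already failed two months of conventional care, with the final area unchanged. Over the assumed range of -10% to +10%, a 50% reduction shifts by -5.6 to +4.5 points. With no difference between arms, the bias is zero.

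On blood results, the conclusion is limited to statements that must be reconciled.

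**What to change.** State in the Study algorithm that the randomisation call is made only when three items are on file: the baseline ulcer photograph, the baseline CIVIQ, and the blood count and serology results needed for eligibility. Add all three to Tables 1 and 2, before or at the randomisation mark, and name that photograph as the baseline for the percent reduction and the covariance models. Day 1 allocation can then stay where booking needs it, and the Day 8 photograph can be kept as a start-of-treatment record.

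Alternatively, if booking allows, move randomisation to Day 8, after the photograph and questionnaire and with the laboratory results on file. This keeps the baseline at the start of treatment.

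The cost is a sentence and a few table marks. Under either option, patients without a recent blood test wait for the result before allocation. Under the first, the measured change includes about one week of common usual care in both arms. Under the second, the Day 8 appointment must be arranged before the arm is known.

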### Protocol

#### Control group

Patients in the control group will be treated as they had been prior to inclusion, that is, two to three times a week and in accordance with the health region recommendations, namely to maintain a moist healing environment. The wound care will consistently be provided by the same nurse, who will be responsible for making the appointments within the available timetable in the treatment room. The data will be registered in an Access database by the administrator. The treatment schedule for the control group is displayed in Tables 1 and 2.

**Table 1 Tab1:** **Timetable for the control group**

**Activities**	**Recruitment Day 0**	**Selection Day 1**	**Day 3**	**Day 5**	**Day 8**	**Day 15**	**Day 22**	**Day 29**	**Day 36**	**Day 43**	**Day 50**	**Day 57**	**Day 64**
Patient recruitment	X												
1^st^ visit		X											
Leg Doppler ultrasound		X											
Informed consent		X											
Randomisation		X											
Inform GP in writing		X											
Conventional treatment		X	X	X									
Autologous PRP treatment					X	X	X	X	X	X	X	X	
Ulcer Assessment					X				X				X
Final Assessment													X

**Table 2 Tab2:** **Timetable for the intervention group**

**Activities**	**Recruitment Day 0**	**Selection Day 1**	**Day 3**	**Day 5**	**Day 8**	**Day 15**	**Day 22**	**Day 29**	**Day 36**	**Day 43**	**Day 50**	**Day 57**	**Day 64**
Patient recruitment	X												
1^st^ visit		X											
Leg Doppler ultrasound		X											
Informed consent		X											
Randomisation		X											
Inform GP in writing		X											
Conventional treatment		X	X	X									
Autologous PRP treatment					X	X	X	X	X	X	X	X	
Ulcer Assessment					X				X				X
Final Assessment													X

Week^(1)^: the wound will be treated every 48 to 72 hours during these weeks, as required in each case (depending on the condition of the ulcer).

Week^(1)^: the wound will be treated every 48 to 72 hours during these weeks, as required in each case (depending on the condition of the ulcer).

### Moist wound care

Patients in the control group will be treated following the recommendations for MWC of Osakidetza (described in the rational use of the moist wound care products section of the Osakidetza 2011 continuous professional education guide). Material is selected for wound care depending on the assessment of the bed of the wound and surrounding skin, as well as the type and amount of exudate and whether there are signs of infection. These wound care treatments will be carried out every 48–72 hours, in line with the current usual practice.

There are multiple types of dressings, each of which have a proposed indication as well as certain known advantages and disadvantages. It is important to recognise that no single dressing is suitable for all types of ulcers and few are indicated for all stages of healing. For a given wound, the ideal dressing should absorb excess exudate, create a moist environment, and maintain an adequate pH, while also being thermally insulating, impermeable to bacteria and easy to change, as well as not causing allergic reactions or damage when removed.

The materials used in the MWC include the following:Debriding agents: enzymatic, mechanical, physiological and autolyticAntimicrobial agents: containing silver, indicated for infected woundsActivated charcoal: for odour controlHydrocolloids: for debridement and promotion of granulation tissue, one of their strengths being that they are not very absorbent.Alginates and hydrofibres: for exudating and contaminated wounds and they also have a hemostatic effect; a disadvantage of alginates being that they are less absorbent than hydrofibresPolyurethane foams: hydrocellular dressings and hydropolymer dressings; the latter are indicated for moderate to high amounts of exudate, but their disadvantages include that they do not absorb exudates or debride the wound in the same way.Barrier products: for preventing maceration and irritation of the skin around the lesion

When selecting a dressing, as well as the characteristics of the wound, it is necessary toassess the general status of the patient, the availability of resources, and the cost-effectiveness of alternatives, as well as how easy it is to apply.

### Intervention group

Patients in the intervention group will receive wound care once a week with autologous PRP, based on the estimated mean lifespan of platelets (7–10 days). The treatment with autologous PRP will be performed in the assigned outpatient clinic, in the phlebotomy room, by qualified nurses ([name]).

As in the control group, the nurse will be responsible for making appointments for the next treatment and will collect data to be entered in an Access database by the administrator. The first treatment session of the study will be performed on day 8, and the data will be recorded in the patient medical record. From this point onwards, data will be collected every 7 days for 9 weeks. Treatment schedule for the PRP group is shown in Table 2.

### Outcome measures

#### Reduction in ulcer size

A main variable, in terms of the difference in the surface area of the ulcer at weeks 5 and 9 of treatment compared to baseline, expressed as the percent reduction in area for each of the patients in the intervention and control groups.

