## Methods and design

### Hypothesis

After 2 months, treatment with PRP will lead to at least a 20% greater reduction in the ulcer area than observed in patients receiving standard care based on the current protocol in PC of moist wound care (MWC).

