### Objectives

#### Primary objectives

To assess the efficacy in healing the ulcers attributable to autologous PRP by estimating the change in the ulcer area using serial photographs, at baseline and 5 and 9 weeks after starting the treatment, compared with that in the control group.

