### Statistical analysis

The categorical variables will be presented as frequencies and percentages (for example, the percentage of patients requiring ≤1 weekly treatment) and continuous variables using measures of central tendency and dispersion (mean and standard deviation for normally distributed variables, and otherwise median and interquartile rank).

The analysis of the efficacy will be carried out on an intention-to-treat basis by comparing the percent reduction in ulcer area, observed in each of the groups after 5 and 9 weeks of treatment, with respect to baseline. Using the Mann–Whitney U non-parametric test, we will estimate the effect attributable to the intervention using the difference between the changes occurring in the two groups.

Subsequently, in order to adjust the comparisons for the baseline measurements, we will carry out covariance analysis models. As well as adjusting for baseline, we will adjust for the potential confounding or effect-modifying covariates. A p value <0.05 will be considered statistically significant.

All the analyses will be performed using SAS version 9.2 statistical software.

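### The hypothesis names one time point, but the objective, main variable and analysis name two visits without ranking them; if either visit could carry the claim, the 5% error would become about 7% to 9%

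*Protocol article*

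**What the plan says.** The Hypothesis section ties the expected effect to one time: "After 2 months, treatment with PRP will lead to at least a 20% greater reduction in the ulcer area".

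Three later sections name two times:

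- Primary objectives: change in ulcer area is estimated "at baseline and 5 and 9 weeks after starting the treatment, compared with that in the control group".
- Outcome measures, Reduction in ulcer size: the main variable is the "difference in the surface area of the ulcer at weeks 5 and 9 of treatment compared to baseline", as a percent reduction.
- Statistical analysis: the arms are compared on the percent reduction "observed in each of the groups after 5 and 9 weeks of treatment", first by the Mann–Whitney U test and then by covariance models that adjust for baseline and other covariates.

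The threshold is given once, without reference to a visit: "A p value <0.05 will be considered statistically significant". The Sample size section uses α = 0.05, 80% power, a 15-point difference and 30% withdrawal, and attaches no visit to the 15 points.

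On dates, the Intervention group section states: "The first treatment session of the study will be performed on day 8". Tables 1 and 2 both schedule the ulcer assessment on Days 8, 36 and 64, and label Day 64 as the final assessment.

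**The concern.** A confirmatory trial that spends one α needs one primary comparison, or a rule for combining several. Here the hypothesis supplies one comparison, while the objective, outcome and analysis supply two of equal standing. Someone reporting the trial could cite the article in support of a claim at the early visit, at the late visit, or at whichever was significant. The last option would raise the false-positive rate above the 5% used in the sample size. The treatment is also open-label, so the visit that carries the claim should be settled before any results are seen.

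A smaller question is whether the week labels agree with the schedule. If they do not, the reported duration of treatment behind the result would be wrong by a week.

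**Working it through.** **Inputs.** Two visits (Primary objectives; Reduction in ulcer size; Statistical analysis). Threshold 0.05 (Statistical analysis; Sample size). Sidedness is not stated, so two-sided is assumed. The correlation between the test statistics at the two visits is not given, so a range is shown.

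**Type I error under three readings.** Let Z1 and Z2 be the test statistics at the two visits, bivariate normal with correlation r under no treatment effect.

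1. Only the 2-month visit is primary: the error is 0.05, the figure used in the sample size.
2. Significance at either visit is enough: the error is 1 − P(|Z1| ≤ 1.96 and |Z2| ≤ 1.96). With r = 0 this is 1 − 0.95² = 0.0975.
3. Both visits must be significant: the error is 0.05 + 0.05 − (result of reading 2).

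| r (assumed) | Either visit | Both visits |
|---|---|---|
| 0 | 0.0975 | 0.0025 |
| 0.5 | 0.0907 | 0.0093 |
| 0.7 | 0.0835 | 0.0165 |
| 0.8 | 0.0781 | 0.0219 |
| 0.9 | 0.0704 | 0.0296 |

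The error therefore exceeds 5% only under reading 2.

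**Does the remedy affect the sample size?** The article gives no SD, so 150 cannot be reproduced. Solving backwards, 75 × (1 − 0.30) = 52.5 evaluable per group, and SD = 15 × √(52.5/2) / (1.960 + 0.842) ≈ 27.4 points. With that implied SD:

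- One primary visit at 0.05: power is 80% and N stays at 150.
- α split to 0.025 per visit: n = 2 × (27.4/15)² × (2.241 + 0.842)², which rounds up to 64 evaluable per group. Then 64/0.70 rounds up to 92 per group, or 184 in total. At N = 150 the power per visit would fall to about 71%.

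**Week labels.** Study treatment starts on Day 8.

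| Assessment | From Day 8 | From Day 1 |
|---|---|---|
| Day 36 | 28 days = 4.0 weeks | 35 days = 5.0 weeks |
| Day 64 | 56 days = 8.0 weeks | 63 days = 9.0 weeks |

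Five and nine full weeks after Day 8 would be Day 8 + 35 = Day 43 and Day 8 + 63 = Day 71. Neither table schedules an ulcer assessment on Day 43, and both end on Day 64.

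**The case against.** The strongest reply is that the hypothesis already settles the matter: it names 2 months only, and of the scheduled assessments only Day 64 fits. A condensed article need not set out the visit hierarchy or the division of α, which an analysis plan commonly provides. The p<0.05 sentence is a general convention, not a success rule. Much of this stands. Silence on α allocation is not the defect. The defect is that the article states the primary time in two incompatible ways, and the sections that define the objective, the main variable and the analysis do not follow the hypothesis.

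A reader might go further and infer that the type I error certainly exceeds 5%. The documents do not support that, because no section says that either visit suffices. A reader might also count the Mann–Whitney test and the covariance models at each visit as four separate chances of success. The Statistical analysis section presents the covariance models as a subsequent adjustment of the same comparison, so that count is not warranted.

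On dates, a reader might infer that the endpoint date is left open. It is not, because both tables fix Days 8, 36 and 64. The main variable's wording can also be read ordinally: counting from Day 8, the 5th treatment week begins on Day 36 and the 9th on Day 64. That reading does not rescue the Primary objectives, which say "at baseline and 5 and 9 weeks after starting the treatment", or the Statistical analysis section, which counts completed weeks of treatment.

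**Conclusion.** The point holds as an inconsistency in the primary time: one time in the hypothesis, two unranked visits in the objective, main variable and analysis, under one unadjusted threshold and one α in the sample size. The consequence is conditional. If either visit may carry the claim, the type I error is about 7.0% to 9.1% for assumed correlations of 0.9 to 0.5, and 9.75% if the visits are independent. It is 5% if the 2-month time alone is primary, and at most 5% if both visits must succeed. These figures assume two-sided tests and bivariate normal statistics.

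The week mismatch is real but minor. It is confined to the wording that counts elapsed weeks, amounts to 7 days at each visit, and applies equally to both arms. It therefore does not bias the comparison or change the test or the sample size.

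**What to change.** In Primary objectives, Reduction in ulcer size and Statistical analysis, name one primary endpoint: percent reduction in ulcer area from baseline (Day 8) to the final assessment (Day 64), tested at two-sided 0.05. State that this is the 2-month time of the hypothesis. List the Day 36 assessment as secondary.

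Use one week origin throughout, for example Day 36 and Day 64 (4 and 8 weeks after the first study treatment). Apply it also in the Secondary objectives, where the quality-of-life score carries the same elapsed-week wording.

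The change is to wording only, and N stays at 150. The one cost is that the early visit can no longer carry the primary claim. If the sponsor wants to be able to claim at either visit, an equal split of α would hold the error at or below 5%, but at about 71% power per visit with 150 patients, or about 184 patients for 80%, both under the implied SD of 27.4.
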